### Interim analyses {21b}

No interim analysis is planned.

### Methods for additional analyses (e.g. subgroup analyses) {20b}

Demographic and other baseline data will be summarised descriptively by a randomised treatment arm. Numbers of complete and missing data (if any) will be shown. Relative frequencies will be shown as valid % (number of patients divided by the number of patients with non-missing values).

### Methods in analysis to handle protocol non-adherence and any statistical methods to handle missing data {20c}

Unless otherwise stated in particular cases, missing values are not replaced and only observed cases are analysed.

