**Secondary**	
The secondary objectives aim to assess the efficacy of TIPS implantation on the course of liver disease and quality of life (QOL)	The following outcome parameters are defined as secondary endpoints: • Time to ascites with need for paracenteses^#^ (Estimand 2) • Quality of life assessed with the SF-36 and CLDQ (chronic liver disease questionnaire) 6 and 12 months after randomisation (Estimand 3)
**Safety**	• Adverse events (AEs), and severe adverse events (SAEs), incidence of complications related to TIPS implantation (incl. technically unsuccessful TIPS implantation) • Rate of TIPS dysfunction • Rate of TIPS implantation in the SMT group

^#^Ascites with need for paracenteses will be classified as following, taking into account the *abdominal distention* caused by ascites [1]: (I): Ascites grade 1(mild): ascites is detectable only by ultrasound examination; (II): Ascites grade 2(moderate): ascites causes moderate symmetrical distension of the abdomen; (III): Ascites grade 3 (severe, large/gross ascites): it causes marked abdominal distension. If patients develop symptoms due to ascites (pain, abdominal tension, dyspnoea), paracentesis should be performed. Date of paracentesis, volume removed and albumin replacement/dose are documented for each paracentesis. Recurrent ascites according to the Baveno VII recommendations is defined as a requirement of 3 or more large-volume (greater than 5 L) paracenteses per year (only paracenteses in stable conditions without infections are considered)[7]

#### Estimand 1

The primary estimand that corresponds to the primary trial objective to show superiority of early implantation of a TIPS in patients with liver cirrhosis and ascites compared to standard medical treatment based on the primary endpoint transplantation-free survival is specified by the following 5 attributes.

*Population:* [A] The population targeted by the primary estimand will be called full analysis set (FAS). This means that the patients will be analysed in the treatment arms to which they were randomised. All randomised patients will be included in the FAS.

*Treatments***:** The randomised experimental arm (TIPS implantation) is compared to the randomised control arm (SMT) of ascites regardless of dosing modifications, treatment interruptions, treatment discontinuation and regardless of intake of additional medications.

Treatment groups are called early TIPS and standard medical treatment.

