### Definition of the secondary estimands

#### Estimand 2

Estimand 2 that corresponds to the secondary trial objective to assess the efficacy of TIPS implantation on the course of liver disease is specified by the following 5 attributes. *Population: [A], Treatments: [A].*

*Variable (endpoint):* The endpoint is ascites with need for paracenteses defined as time from randomisation to date of paracentesis.

*Intercurrent events*: transplantation, death will be considered as competing events.

*Population-level summary:* The population-level summary is defined by the statistical analysis approach which is described below.

#### Estimand 3

Estimand 3 that corresponds to the secondary trial objective quality of life is specified by the following 5 attributes.

*Population [B,C]:* 6, 12-month survival of FAS *Treatments:* [A].

*Variable (endpoint):* The endpoint is quality of life measured by SF-36 and CLDQ.

*Intercurrent events:* There are no intercurrent events not already addressed by the specification of population, treatments and variables.

*Population-level summary:* The population-level summary is defined by the statistical analysis approach which is described below.

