## Data collection and management

### Plans for assessment and collection of outcomes {18a}

Examinations and assessments will be performed at pre-defined timepoints as specified in Table 2. Data will be entered by the investigator/authorised personnel in the eCRF (REDCap® system). Questionnaires (SF-36 and CLDQ) are first filled out on paper and then transferred to the eCRF. At each visit, patient life status, liver transplantation and paracentesis performed are queried. Events related to TIPS implantation during and after the end of the procedure, categorised incidences for all patients and all other adverse events are collected in a patient safety form in the eCRF.

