## Statistical methods

### Statistical methods for primary and secondary outcomes {20a}

The following populations for analyses are defined: (I) The population targeted by the primary estimand will be called full analysis set (FAS). This means that the patients will be analysed in the treatment arms to which they were randomised. All randomised patients will be included in the FAS. (II) The safety set (SAF) includes all randomised patients who underwent TIPS procedure or received SMT, and patients are analysed according to the received treatment.

The estimand and competing events are described above and summarised in Table 4.

**Table 4 Tab4:** Estimand and competing events

(Intercurrent) events	Time to	
	**Transplantation free survival**	**Ascites with need for paracenteses**
**Transplantation**	Event	Competing
**Ascites with need for paracenteses**	Ignore	Event
**Death**	Event	Competing
**TIPS implantation**	Ignore	Not available/event
**TIPS revision**	Ignore	Not available/event

The effects of SMT and TIPS implantation with respect to the primary endpoint transplantation-free survival will be estimated and tested by Cox regression. The regression model will include treatment and study site as independent variables, as well as baseline bilirubin, creatinine and age. As an estimate of the effect size, the hazard ratio between the two treatment arms will be given with the corresponding asymptotic two-sided 95% confidence interval. The two-sided test on the difference between SMT and TIPS at significance level 5% will be based on the corresponding asymptotic two-sided 95% confidence interval from the Cox regression model.

The effects of SMT and TIPS implantation with respect to the secondary endpoint time to ascites with need for paracenteses will be estimated and tested by Cox regression. The probability of event over time will be estimated by cumulative incidence rates due to competing events, transplantation and death. The time to event will be compared between the treatment groups with Cox regression models for the event-specific hazard functions using two-sided Wald tests. The regression model will include treatment and study site as independent variables, as well as baseline bilirubin, creatinine and age. As an estimate of the effect size, the event-specific hazard ratio between the two treatment arms will be given with the corresponding asymptotic two-sided 95% confidence interval.

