SF-36 and CLDQ will be compared between treatment arms at two different timepoints (months 6, 12). At both timepoints, a mixed linear model for repeated measures (MMRM) is used modelling the respective scale at this and the earlier timepoints, and including randomised treatment and the baseline value of the respective subscale and centre as covariates. Two-sided *p* values of the tests of the hypotheses that the treatment effect is zero at the respective timepoints will be calculated from these models. As estimates of the effect sizes, the differences of adjusted means (TIPS arm vs.SMT arm) will be calculated with two-sided 95% CI.

The total number of AEs, the minimum, maximum and mean number of adverse events (AEs) per patient, the total number of follow-up (FU) days (number of days in the observation period), the number of AEs per FU-day (total number of AEs divided by the total by the number of follow-up days), the number of patients who had at least one AE and the number of patients who stopped treatment due to AE will be given.

The probability of AEs defined by preferred term (PT) according to MedDRA and of AEs defined by system organ class (SOC) according to MedDRA will be estimated by the Aalen-Johansen estimator. For this purpose, the time from randomisation to the first occurrence of the specific type of AE (defined by PT or defined by SOC) will be analysed. For patients not experiencing the specific type of AE, the time to the end of the documentation period or death, whatever occurs first, will enter the analysis and will be treated as a competing event. This will result in probability estimates (cumulative incidences) for the different AE types (defined by PT and by SOC) over time. The results will be displayed in summary tables by showing the cumulative incidences at the maximum observation time. Incidences of AEs will be calculated with 95% confidence intervals. Additionally, the number of non-serious AEs will be summarised by PT and by SOC.

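### As written, the observed-cases rule would drop patients without a baseline SF-36 or CLDQ score from the quality-of-life model, together with their observed follow-up scores

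*Protocol article*

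**What the plan says.** The general rule is in the protocol article, section {20c}. After an opening clause that admits exceptions stated elsewhere, it reads: "missing values are not replaced and only observed cases are analysed". It is thus a default that leaves room for exceptions. The article names none for baseline covariates.

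Section {20a} specifies the models. For SF-36 and CLDQ at months 6 and 12 it plans a mixed linear model for repeated measures, "including randomised treatment and the baseline value of the respective subscale and centre as covariates". For both time-to-event endpoints it plans Cox regression: "The regression model will include treatment and study site as independent variables, as well as baseline bilirubin, creatinine and age".

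The populations differ by endpoint. Estimand 1 (transplantation-free survival) targets the full analysis set, of which section {20a} says "All randomised patients will be included in the FAS". Estimand 3 (quality of life) is narrower; its population is given as "6, 12-month survival of FAS".

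On collection, section {18a} says: "Questionnaires (SF-36 and CLDQ) are first filled out on paper and then transferred to the eCRF". Table 3 schedules the two questionnaires at screening, month 6 and month 12.

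**The concern.** A regression fitted to observed cases cannot use a patient who lacks one of its covariates. Applied to the quality-of-life model, the default means that one missing baseline questionnaire also removes that patient's month 6 and month 12 scores. The baseline value is there to improve precision, so losing observed outcomes for want of it defeats its purpose.

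It also works against the choice of model. Section {20a} models each timepoint jointly with the earlier one, so that a patient with only part of the follow-up can still contribute. Requiring an observed baseline takes that benefit away from anyone without one. The set analysed would then be smaller than the surviving patients whom Estimand 3 names.

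**Working it through.** **Can a patient be randomised without a baseline score?** Yes, on the text.
- Section {16a} allows randomisation only after eligibility has been confirmed.
- Table 1 lists neither SF-36 nor CLDQ among the eligibility criteria.
- The questionnaires are due only once before randomisation, at screening (Table 3), and are completed on paper (section {18a}).
- The trial is open, so a form completed after allocation is not an equivalent substitute.

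None of this shows that forms will be missing, only that nothing in the randomisation step prevents it.

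**Size for quality of life.** The article gives no missing-baseline rate, so the share m is assumed. The variance of a difference in adjusted means is roughly proportional to 1/n. Dropping a share m in both arms multiplies the standard error by 1/√(1 − m).

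| m (assumed) | 1/√(1 − m) | Rise in standard error |
|---|---|---|
| 5% | 1/√0.95 = 1.026 | 2.6% |
| 10% | 1/√0.90 = 1.054 | 5.4% |
| 20% | 1/√0.80 = 1.118 | 11.8% |

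These are upper figures for what the remedy could recover. They treat every dropped patient as having complete follow-up scores, and they treat the remedy as restoring full information. In practice a patient without a baseline form may also lack later ones, and a mean-filled baseline does not give back that patient's own covariate adjustment.

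The same shares of all 134 randomised patients would be 0.05 × 134 = 6.7, 0.10 × 134 = 13.4 and 0.20 × 134 = 26.8. The estimand covers survivors only, so these counts are ceilings.

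**Size for the primary Cox model.** The plan's own figure comes first. The assumed one-year rates give HR = ln 0.82 / ln 0.66 = 0.478, with |ln HR| = 0.739. Schoenfeld's formula gives 4 × (1.96 + 0.8416)² / 0.739² = 57.5 events, close to the stated 57. Power at 57 events is Φ(√(57/4) × 0.739 − 1.96) = 79.7%, against the stated 80%.

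If 2% of patients lacked a covariate (assumed), 57 × 0.98 = 55.9 events would remain, and power would be Φ(√(55.9/4) × 0.739 − 1.96) = 78.9%. With HR rounded to 0.48, the corresponding values are 79.1% and 78.3%. The shift is about 0.8 points either way.

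Even 2% is probably too high. Age is an inclusion criterion and bilirubin an exclusion criterion (Table 1), so both must be known before randomisation. Creatinine should come with the screening clinical chemistry, and with the MELD score recorded at screening (Table 3), assuming MELD is calculated with creatinine as usual. MELD decides eligibility only for grade 2 ascites, so creatinine is slightly less protected than the other two.

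**Bias.** The baseline form is due before randomisation. If it is completed then, whether it is missing cannot depend on the arm, and in expectation both arms lose the same share.

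**The case against.** The strongest reply is that section {20c} is only a default, that it expressly admits exceptions, and that the handling of a missing baseline covariate is normally settled in the statistical analysis plan or the full protocol, neither of which is at hand. This stands in part. If either document already states an exception, the sponsor need only confirm it. But the article is not silent. It fixes a rule, and that rule, applied to the model in section {20a}, discards observed outcomes.

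A second reply is that the size rests wholly on assumed missingness, and that questionnaires scheduled at screening for every patient may be nearly complete. This stands too: at a rate close to zero the point has no practical effect.

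A reader might go further and infer any of the following. The article does not support them.
- *That the rule removes patients from the primary analysis and so contradicts the full analysis set of all randomised patients.* The conflict exists in principle, but it arises only if a Cox covariate is missing, and the eligibility and screening requirements make that rare.
- *That the quality-of-life analysis must include all randomised patients.* Estimand 3 is limited to survivors at 6 and 12 months, and that is the population to compare against.
- *That quality-of-life power falls from 80% to some lower figure.* The sample size section {14} powers transplantation-free survival only. No power for quality of life is stated, so there is no starting value from which to measure a fall.

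**Conclusion.** The point holds as a minor one, confined in practice to quality of life. Under the stated default, surviving patients without a baseline SF-36 or CLDQ score leave the mixed model even when their follow-up scores are observed. For 5% to 20% missing baseline, the standard error rises by at most about 2.6% to 11.8%. The effect on the primary Cox model should be near zero, and no figure stated in the article changes.

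The conclusion rests on three assumptions: that the missing share lies in that range, which the article does not give; that baseline forms are completed before allocation, so that the loss is one of precision and not a bias between arms; and that no exception is already written in a document not shown here.

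**What to change.** Use the exception clause of section {20c}, in the protocol or the analysis plan. State that missing baseline SF-36 and CLDQ scores, and any rare missing baseline bilirubin or creatinine, are replaced by the overall mean of that variable calculated without regard to arm. For the quality-of-life model an equally good alternative is to enter baseline as a response with a common mean across arms. State also that outcomes after baseline remain unimputed.

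Either version keeps in the model every patient in the estimand's population who has an observed follow-up score. The choice should be fixed before outcome data are examined, so that it is not made after the fact. The cost is one sentence and negligible programming, with no new data.

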### Plans to give access to the full protocol, participant level-data and statistical code {31c}

The sponsor assures that the key design elements of this protocol will be posted in a publicly accessible clinical trials registry.

### Composition of the data monitoring committee, its role and reporting structure {21a}

An independent Data Monitoring Committee (DMC) is established. The DMC consists of two independent physicians (one interventional radiologist with experience in TIPS implantation and one hepatologists with longterm experience in treatment of patients with portal hypertension) and a statistician. The function of the DMC is to monitor the course of the trial and if necessary to give a recommendation to the coordinating investigator for continuation, modification or discontinuation of the trial. The underlying principles for the DMC are ethical and safety aspects for the patients. It is the task of the DMC to examine whether the conduct of the trial is still ethically justifiable, whether the safety of the patients is ensured, and whether the process of the trial is acceptable. For this, the DMC has to be informed about patient recruitment, adherence to the protocol and observed adverse events. A continuous safety survey of the study will be conducted as part of the annual DMC meetings. The DMC will evaluate mortality, frequency and type of SAEs taking into consideration discontinuation criteria.

### Adverse event reporting and harms {22}

An adverse event (AE) in this study is defined as any untoward medical occurrence/complication in a patient who underwent TIPS or received SMT and which does not necessarily have to have a causal relationship with the TIPS implantation or received therapy.

Table 5 summarises the parameter/adverse events that will be documented to monitor interventional and SMT safety.

**Table 5 Tab5:** Parameter/adverse events that will be documented to monitor interventional and SMT safety

**During TIPS procedure**	**After the end of the procedure AEs related to TIPS implantation**	**For all patients **
• Injury to carotid artery (perforation) • Procedural pneumothorax • Injury to hepatic artery (perforation/puncture) • Liver capsule perforation • Bile duct injury • Arrhythmia • Allergic reaction • Injury to surrounding organs • Intra-abdominal bleeding • Other	• Complications related to the shunt: – TIPS thrombosis – TIPS dysfunction • Contrast media toxicity • Fistula formation • Other directly related to TIPS procedure	• Bleeding oesophageal varices • Hepatic encephalopathy (HE) beginning from grade II [25] • Spontaneous bacterial peritonitis (SBP) • HRS-AKI • Acute kidney injury (AKI) • Acute on chronic liver failure (ACLF) • Diuretic-induced complications • Cardiac failure (according to NYHA class) • Ischemic hepatitis • Infections • Hepatocellular carcinoma (HCC) (including at least BCLC staging, tumor diameter, vascular invasion etc.) • Other

Adverse events have to be documented in the eCRF starting from the date of ICF signature and until end of the study with the following information: characterisation of the event (listed complication, see above [diagnosis or symptoms, if diagnosis not yet available]), onset/end date, severity according to the current version of CTCAEv5, relationship to procedure (yes/no) or to the shunt (yes/no), serious/non-serious and outcome.

### Frequency and plans for auditing trial conduct {23}

Monitoring is performed by the clinical research associates (CRAs) of the CTU, Medical Center—University of Freiburg. Risk-based monitoring will be conducted according to ICH-GCP E6 and standard operating procedures (SOPs) to verify that patients’ rights and well-being are protected, reported trial data are accurate, complete and verifiable from source documents and that the trial is conducted in compliance with the currently approved protocol/amendment, with ICH-GCP E6 and with the applicable regulatory requirements to ensure patient safety and integrity of clinical trial data.

The investigator will accept monitoring visits before, during and after the clinical trial. Prior to the trial, a site selection visit at each site is conducted to check the prerequisite of the team. Prior to patient recruitment, a site initiation visit at each site is conducted in order to train and introduce the investigators and their staff to the trial protocol, essential documents and related trial-specific procedures, ICH-GCP E6 and national/local regulatory requirements.

On the basis of a risk-based quality management process, the CRA will visit the site regularly depending on trial risk (in this case: low risk) and depending on the recruitment rate and quality of data. During these on-site visits, the CRA verifies that the trial is conducted according to the trial protocol, trial-specific procedures, ICH-GCP, international and national/local regulatory requirements, as applicable. The CRA also performs source data verification and source data review to ensure that the clinical trial data which are recorded in the source data and eCRFs are complete and accurate and to ensure the smooth flow of the processes which are agreed.

In addition to on-site visits, off-site visits can be carried out as long as the centre’s data quality permits (after consulting the project manager and coordinating investigator).

All trial-specific monitoring procedures, monitoring visit frequency and extent of source data verification will be predefined in a trial-specific monitoring plan. The investigator must maintain source documents for each patient in the trial, consisting of case and visit notes (hospital or clinic medical records) containing demographic and medical information, laboratory data, electrocardiograms and the results of any other tests or assessments. All information recorded on eCRFs must be traceable to source documents in the patient’s file. The investigator must also keep the original signed informed consent form (a signed copy is given to the patient).

The investigator must give the CRA direct access to all relevant source documents to confirm their consistency with the eCRF entries and document any protocol violation including corrective and preventive actions taken on a protocol deviation form as soon as possible.

The study may be audited at any time, with appropriate notification, by qualified personnel from the sponsor or an independent external party, to assess compliance with the protocol, good clinical practice (GCP) and regulatory requirements. The study may also be inspected by health authority inspectors, after appropriate notification. The investigator needs to inform the CTU immediately of an inspection requested by a regulatory authority. In the event of an audit or an inspection, the investigator should ensure that direct access to all study documentation/data, including source documents, will be granted to the auditors or inspectors.

